#### Statistical criteria of termination of trial

There is no statistical criteria for termination of trial. An interim statistical analysis will be performed after the first three months, but given the frequent changes of the epidemiological situation, the final statistical analysis (after six months of intervention) will be performed independently by results of the interim analysis.

#### Planned analyses

##### Datasets to be analysed, analysis populations

The analysed population consisted of pupils and students of kindergartens, primary and secondary schools located in Italy, Portugal, Germany and Mexico.

##### Primary analysis (LM evaluation trial)

The number of clusters per class per week will be compared between the two arms: LM + SoC arm vs SoC only. Absolute and relative frequencies of clusters will be reported by arms and compared at univariate analysis with Chi Square or Fisher exact test, as appropriate. Univariate analysis will be performed and the p-values for statistical tests of associations of categorical and continuous variables with the two treatment arms will be reported (Chi square/Fisher exact test and T-test/Wilcoxon sum rank test for categorical and continuous variables, respectively). We will also investigate the psychological impact of Lolli tests and preventive measures to reduce the risk of infections; we will compare the frequency of infections according to socio-economic status, regions, teacher vs student, educational level, also taking into account vaccination rates within each class.

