### Study design

#### General study design (Fig. 1)

**Fig. 1 Fig1:**
[figure not shown]
Study flowchart. The flowchart summarize the general study where is divided in two sub studies, (i) interventional study which contains a Lolli arm and a control arm; and (ii) observational study. A detailed description have been written in the main text. We want to acknowledge Pez Beta Design for the elaboration of the figure

A multicenter cluster randomised interventional study will be set-up to evaluate the efficacy and applicability of the LM. The study will enrol 440 classes (around 8800 students, teachers and other personnel). Statistical units are represented by classes, randomized to LM or SoC.

The study will be carried out for 6 months, from October 2022 to March 2023 and includes two saliva tests a week. We assume that in the course of the investigated period the incidence rate of SARS-CoV-2 infection will change and this will allow us to test our hypotheses under different epidemiological conditions.

The randomisation will be applied as cluster randomisation: classes will be randomised in each school to the adoption of the LM or to SoC with contact tracing activity by public health departments and regular surveillance based on symptoms indicating testing. The two groups of classes will be compared in order to assess whether the LM will reduce the frequencies of attack rates/clusters dimension compared with classes on SoC. Logistics and costs affordability will also be evaluated.

An observational retrospective and prospective study will be carried out to investigate the prevalence of SARS-CoV-2 in schools with different variants, frequencies and size of clusters and attack rates in schools, the effect of different NPIs on SARS-CoV-2 diffusion in the schools and the related psychological effects. The study will involve classes/schools that are not involved in the interventional randomised study.

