### Statistical methods

#### Hypothesis

The main hypothesis is that the LM can reduce the frequency of clusters (i.e. two or more cases in a class within a scholar week).

The main endpoint is the frequency of cluster per class in a scholar week.

Secondary endpoints are cluster size and duration of consecutive/serial infections in the same class.

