##### Secondary analyses (ancillary observational study)

Univariate and multivariable analyses will be carried out to identify other independent factors associated with the presence of clusters per class per week (yes vs no) with logistic regression models, adjusting for possible confounding variables. Individual infection (infected vs/not infected per week and in the whole study period) will be also evaluated with logistic regression models, adjusting for possible confounding variables and also comparing teachers and students. Finally, we will evaluate time from the trial start to first cluster with survival analyses.

Random effects models for repeated measures will be carried out to investigate independent factors associated with psychological scores, taking into account of confounding factors such as age, sex, vaccination status, socio-economic status, different use of preventive measures, and extra-scholar activities.

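### The primary chi-square/Fisher test is set on clusters per class per week, but the class is the randomised and sized unit; repeated weeks of one class would be treated as independent

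*Protocol article*

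**What the plan says.** Under General study design the unit is explicit: "Statistical units are represented by classes, randomized to LM or SoC". The same section says that "classes will be randomised in each school to the adoption of the LM or to SoC", and gives the duration: "The study will be carried out for 6 months, from October 2022 to March 2023".

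Determination of sample size follows that unit. It compares two proportions in 220 classes per arm, with a one-sided pooled Z test at 5%.

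The endpoint has a different unit. Under Hypothesis, a cluster is two or more cases in a class within one school week, and "The main endpoint is the frequency of cluster per class in a scholar week". The Primary analysis section keeps the weekly unit ("The number of clusters per class per week will be compared between the two arms: LM + SoC arm vs SoC only") and says that cluster frequencies will be "compared at univariate analysis with Chi Square or Fisher exact test, as appropriate".

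No class-level variance is named for this endpoint. Random effects for repeated measures appear only for the psychological scores, and Handling of missing data and drop-outs adds only adjustment and stratification for response rates.

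**The concern.** Chi-square and Fisher tests need independent observations. Six months of follow-up gives each class many weekly values, and two features of the protocol suggest these are linked. Classes differ lastingly: randomisation is stratified by age group, and vaccination and response rates per class are to be taken into account. Outbreaks can also run from one week into the next, since a secondary endpoint is the "duration of consecutive/serial infections in the same class".

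If class-weeks form the rows of the table, the variance is taken below the level at which treatment was allocated. A few classes with long outbreaks falling by chance in one arm could then produce a nominally significant difference. The primary p-value and any interval derived in the same way would be too optimistic.

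**Working it through.** **1. The plan's own sample size.** Inputs from Determination of sample size: 4%, a difference of 3.5 points (so 0.5%), one-sided 5%, 80% power, pooled Z.

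n = [1.645·√(2·0.0225·0.9775) + 0.8416·√(0.04·0.96 + 0.005·0.995)]² / 0.035² = (0.3450 + 0.1753)² / 0.001225 ≈ 221 per arm. Power at 220 is 79.85%.

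The stated 220 is therefore reproduced with each class counted once. (The printed alternative of 0.05% gives 157 per arm; that is a separate point.)

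**2. What the weekly endpoint implies.** The protocol gives six months but no number of school weeks. I assume 24, with a range of 20 to 26. Pooled class-weeks: 220 × 24 = 5,280 per arm, 10,560 in all, from 440 randomised units.

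**3. Error of a pooled test by within-class correlation ρ.** The documents give no ρ, so it is an assumption. Design effect DE = 1 + (24 − 1)ρ. True one-sided error = 1 − Φ(1.645/√DE); two-sided = 2[1 − Φ(1.96/√DE)].

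| ρ | DE | one-sided | two-sided |
|---|---|---|---|
| 0 | 1.00 | 5.0% | 5.0% |
| 0.01 | 1.23 | 6.9% | 7.7% |
| 0.02 | 1.46 | 8.7% | 10.5% |
| 0.05 | 2.15 | 13.1% | 18.1% |
| 0.10 | 3.30 | 18.3% | 28.1% |

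With 20 or 26 weeks at ρ = 0.05, the one-sided error is 11.9% or 13.6%. A beta-binomial simulation at 24 weeks and a weekly rate of 4% gave 13.4% one-sided and 18.1% two-sided at ρ = 0.05.

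**4. Which ρ is plausible.** If classes differ in their weekly rate p with coefficient of variation CV, and nothing carries over between weeks, then ρ = CV²·p/(1 − p).

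| weekly rate p | CV 0.5: one-sided error | CV 1.0: one-sided error |
|---|---|---|
| 0.5% | 5.2% | 6.0% |
| 1% | 5.5% | 6.9% |
| 4% | 7.0% | 12.0% |

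For example, p = 4% and CV 1.0 give ρ = 0.0417, DE = 1 + 23 × 0.0417 = 1.96 and error 12.0%. Carry-over adds to this: with a 10-30% chance that a cluster week is followed by another, and CV 0.5-1.0, simulated one-sided error was 7% to 16%. The top of the range, about 16-18%, needs a 4% weekly rate, CV 1.0 and 30% carry-over together.

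**5. Analysis at class level.** With one value per class, simulated error in the beta-binomial scenarios was 4.8-5.2% one-sided and 4.6-5.2% two-sided for ρ from 0 to 0.20.

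**6. Why the unit in the sample size matters.** The section does not say what period the 4% covers. If it were a weekly class rate, the chance of at least one cluster week in 24 independent weeks would be 1 − 0.96²⁴ = 62.5%. If it were a six-month class proportion, the weekly rate would be about 1 − 0.96^(1/24) = 0.17%. These describe very different trials.

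**The case against.** - **Pooling is not stated.** A reader might infer that the protocol prescribes one table of about 10,500 class-weeks. It does not; that count is arithmetic on an assumed 24 weeks. The test could be run on one yes/no per class, or week by week with each class once per table, and either would be valid for that table. This stands as a limit on certainty. Neither alternative is written, however: the first drops the weekly endpoint, and the second leaves open how the weeks combine. The t-test/Wilcoxon option in the same section could serve a per-class rate, but the sentence on cluster frequencies names chi-square/Fisher.
- **The inflation may be small.** With a low weekly rate and no carry-over it is. Positive cases stay home, confirmed cases are excluded for at least 21 days, containment measures apply to the class, and fewer susceptible pupils remain. All of this could reduce repeat clusters. It stands, and it is why the range starts at about 5%.
- **Randomisation within school protects.** Only in part. School-week effects shared by both arms caused no inflation in simulation (4.3% one-sided). Adding a class effect (SD 1 on the logit scale) gave 15.6%.
- **LM will be declared effective too often.** A reader might infer a bias towards LM. The error is symmetric. One-sided 5% appears only in the sample-size section; with a two-sided test, half of the two-sided error falsely favours LM and half SoC.
- **The later logistic models.** The plan for "presence of clusters per class per week (yes vs no) with logistic regression models" might seem to share the fault. That section is headed as ancillary and names only the model; how its standard errors are computed is commonly left to the SAP, so no point is made of it.

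**Conclusion.** The point holds. The protocol names a primary test that, on the natural reading of its weekly endpoint, does not respect the randomised class, and the sample size and the analysis use different units. This is a stated method, not a detail left to the SAP.

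The direction is certain only if weeks of one class are positively correlated; the protocol's own interest in serial infections makes that likely. The size is not certain. It rests on an assumed 24 weeks and on assumed weekly rates, class differences and carry-over. The documents do not support quoting a single inflated error rate.

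**What to change.** In Primary analysis (LM evaluation trial), replace the class-week chi-square/Fisher test by one of these:

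- One value per class: cluster weeks over school weeks observed. Compare arms by a permutation test that follows the actual randomisation, or by a Poisson or negative binomial model with log(weeks observed) as offset and robust variance.
- A class-week GEE or mixed logistic model with class as the cluster.

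Report the effect with its 95% confidence interval from the chosen method.

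In Determination of sample size, state which class-level quantity, over which period, the 4% and the alternative proportion describe, so that sizing and analysis share a unit. If the outcome is one yes/no per class at 4% versus 0.5%, 220 per arm still gives 79.9% power and no more classes are needed. If it is a rate over weeks, power must be recalculated on that scale.

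The cost is a short rewrite of two sections, a little more analysis work and a wider confidence interval. No new data are required.

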#### Assignment to study groups

Classes will be assigned to the study arms with a randomised web-based procedure: the web randomisation module will accept as input the school-class identifier and will provide as output the study arm, based on a randomisation list balanced by four.

The randomisation will be stratified according to age classes (e.g. kindergarten age; primary intermediate school 6–13 years; secondary school).

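### The primary chi-square/Fisher test on clusters per class per week ignores the correlation between repeated weeks of the same randomised class, so the 5% level is not held

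*Protocol article*

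**What the plan says.** All places are in the protocol article.

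- **General study design:** "Statistical units are represented by classes, randomized to LM or SoC". Follow-up is six months, October 2022 to March 2023, and "classes will be randomised in each school to the adoption of the LM or to SoC".
- **Hypothesis:** a cluster is "two or more cases in a class within a scholar week", and "The main endpoint is the frequency of cluster per class in a scholar week".
- **Primary analysis (LM evaluation trial):** cluster frequencies in each arm are to be "compared at univariate analysis with Chi Square or Fisher exact test, as appropriate". The quantity that enters this comparison is weekly: "The number of clusters per class per week will be compared between the two arms: LM + SoC arm vs SoC only".
- **Secondary analyses (ancillary observational study):** other factors are to be related to the "presence of clusters per class per week (yes vs no) with logistic regression models, adjusting for possible confounding variables". Individual infection, per week and over the whole period, is also modelled by logistic regression. Random effects for repeated measures are named only for the psychological scores.
- **Handling of missing data and drop-outs:** the analysis adjusts and stratifies for response rates. Correlation between weeks is not mentioned.

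**The concern.** The randomised unit is the class, but the unit of the endpoint is the class-week. A chi-square or Fisher table of cluster frequency by arm then has about 24 rows for each randomised class and treats them all as independent.

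They are unlikely to be independent. Pupils, room, vaccination level, age group and willingness to be tested largely persist from week to week. The Hypothesis section itself makes the duration of serial infections within a class a secondary endpoint, so outbreaks that span weeks are expected. Positive correlation within a class makes the real variance of the arm difference larger than the variance these tests assume.

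The trial's main conclusion is at stake. A p-value below 5% could arise well above 5% of the time with no effect of pooled testing, and the error could support twice-weekly screening in schools.

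**Working it through.** **1. The plan's own figure.** Determination of sample size gives 220 classes per arm, 80% power, a 3.5-point difference from 4%, and a one-sided 5% Z test with pooled variance. A 3.5-point difference means 4% against 0.5%.

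- Pooled proportion 0.0225; pooled SD term sqrt(2 x 0.0225 x 0.9775) = 0.2097.
- SD term under the alternative sqrt(0.04 x 0.96 + 0.005 x 0.995) = 0.2083.
- z = (0.035 x sqrt(220) - 1.645 x 0.2097) / 0.2083 = 0.836, so power is 79.9%.

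The stated 80% is reproduced. (The printed 0.05% would give 90.5%; that is a separate matter.) This calculation has one row per class and 440 rows in all, so its unit differs from that of the endpoint and of the primary analysis.

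**2. Rows in the primary table.** Six months is about 26 calendar weeks. Allowing for holidays, I assume m = 24 school weeks: 440 x 24 = 10,560 rows (11,440 at 26 weeks).

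**3. Effect of the correlation.** The article gives no within-class correlation rho, so a range is assumed. The formulas are:

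- design effect DEFF = 1 + (m - 1) x rho;
- understatement of the standard error = sqrt(DEFF);
- true two-sided level = P(|Z| > 1.96 / sqrt(DEFF));
- true one-sided level = P(Z > 1.645 / sqrt(DEFF)).

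Example for rho = 0.05: DEFF = 1 + 23 x 0.05 = 2.15, sqrt = 1.47, and 1.96 / 1.466 = 1.337, so the two-sided level is 18.1%.

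| rho (assumed) | DEFF | SE factor | True level, nominal two-sided 5% | True level, nominal one-sided 5% |
|---|---|---|---|---|
| 0 | 1.00 | 1.00 | 5.0% | 5.0% |
| 0.01 | 1.23 | 1.11 | 7.7% | 6.9% |
| 0.02 | 1.46 | 1.21 | 10.5% | 8.7% |
| 0.05 | 2.15 | 1.47 | 18.1% | 13.1% |
| 0.10 | 3.30 | 1.82 | 28.1% | 18.3% |

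At rho = 0.05, 20 weeks gives 16.1% two-sided and 26 weeks gives 19.1%.

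**4. Check by simulation.** Beta-binomial data were generated with 220 classes per arm, 24 weeks, a weekly cluster frequency of 4% (assumed), no effect and 10,000 replicates. The two-sided rejection rates for rho = 0.01, 0.02, 0.05 and 0.10 were 7.7%, 10.7%, 18.7% and 27.8%. With a frequency of 0.5% they were 7.9%, 10.4%, 18.5% and 28.6%, so the result does not hang on the assumed rate.

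**5. Does randomisation within schools protect the test?** Assuming 55 schools with four classes per arm each (55 x 8 = 440), school-level variation alone gave 4.2% to 4.6%, which is no inflation. Class-level variation did inflate the level: about 9% to 10% with a logit SD of 0.5, and about 23% to 26% with an SD of 1.0.

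**6. After correction.** In the simulations of step 4, one summary per class (mean weekly rate by t-test, or any cluster yes/no by chi-square) gave 4.6% to 5.4% two-sided and 4.3% to 5.4% one-sided for rho from 0 to 0.10.

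**The case against.** **The row unit is inferred.** The design section calls the class the statistical unit, and the sample size counts one proportion per class with a Z test equivalent to an uncorrected chi-square. With 440 rows the test would hold its level. That is true, but it is not what the Hypothesis and Primary analysis sections state. Both say per class per week, and the secondary analyses record a cluster as yes or no per class-week. Nothing collapses the weeks. If one row per class was intended, those sections still need correcting.

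**Such detail may belong in a SAP.** The article does not leave the primary test open. It names one, and that test does not fit the stated endpoint and randomised unit. The argument has more force for the secondary logistic models, which do not exclude robust standard errors and sit under the ancillary study. They are a lesser extension of this point.

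**The size is uncertain.** This stands in part. No correlation is given, and inflation is nil at zero. The sample size section states a one-sided test, for which the inflation is smaller. The 4% has no weekly time base in the article. Exclusion of confirmed cases for at least 21 days, and temporary immunity, could offset some positive correlation. Randomisation within schools removes the school-level part. Lasting differences between classes remain, and a correlation of 0.01 to 0.02 already takes the two-sided level to about 8% to 10%.

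**Conclusion.** The concern holds. As written, the primary test treats repeated weeks of a class as independent, and no other section of the article corrects this. The true level of a nominal two-sided 5% test is about 8% at a within-class correlation of 0.01 and about 28% at 0.10; one-sided, it is about 7% and 18%. These sizes are illustrative. They rest on 24 school weeks, an assumed correlation range, and correlation that is constant across weeks within a class. The direction does not depend on the exact values: any positive correlation inflates the level, and the picture is similar at 20 to 26 weeks. Because it affects the error rate of the main comparison, it must be fixed before analysis.

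**What to change.** State the unit of the primary analysis and use one of these:

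1. **Class-level summary:** one value per class, such as clusters divided by school weeks observed, compared 220 with 220.
2. **Class-week model:** a GEE or mixed-effects logistic or Poisson model with arm and calendar week as covariates and class as the cluster (robust variance or random effect).

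Under either option, adding school and age stratum would reflect the randomisation. Keep chi-square and Fisher tables as description only. State whether the test is one- or two-sided, and tie the rates in the sample size section to the same unit and time base as the endpoint.

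In the secondary logistic models, add a class-level term for class-weeks, and class and school terms for individuals.

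The cost is wording in the protocol and SAP. No extra classes or data are needed for the change itself. Confidence intervals will be wider than those from the class-week table, but they will have the right coverage.

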##### Secondary analyses (ancillary observational study)

Univariate and multivariable analyses will be carried out to identify other independent factors associated with the presence of clusters per class per week (yes vs no) with logistic regression models, adjusting for possible confounding variables. Individual infection (infected vs/not infected per week and in the whole study period) will be also evaluated with logistic regression models, adjusting for possible confounding variables and also comparing teachers and students. Finally, we will evaluate time from the trial start to first cluster with survival analyses.

Random effects models for repeated measures will be carried out to investigate independent factors associated with psychological scores, taking into account of confounding factors such as age, sex, vaccination status, socio-economic status, different use of preventive measures, and extra-scholar activities.

##### Artificial intelligence (AI) based analysis

An evaluation will be carried out to study if and how NPIs applied within the vicinity of the schools in the EuCARE study, variations in mobility and variables that might be linked to the disease spread have affected the outcomes of the study. This will be answered by evaluating treatment bias within the trial and between the control SoC arm and the prospective study.

We will stratify the results by the potential effect modifiers—different class characteristics, NPIs, variation in mobility and variables related to disease spread and evaluate their influence on the study results.

Additional analysis will check whether the outcome of the school studies can be predicted from the mutation prevalence information, the preventive measures and population data during the trial and if yes, what can be learned from these associations. This will be accomplished by training a prediction algorithm taking the class characteristics, mutation prevalence, preventive measures and whether the LM was applied or not, and predicting the number and size of infection clusters during follow-up. If such a model would result with satisfying accuracy levels, then a post-hoc analysis for interpreting interaction associations between the measures included in the model will be provided and an importance analysis on the model features will be executed.

